## Methods

### Study Design

For RCT1, 44 participants will be randomized to 1 of the 2 groups (“HABIT-ILE@home” or “HABIT-ILE on-site camp,” 65 h for 2 wk), 22 children per group (Figure 1). The HABIT-ILE on-site camp will take place in Belgium with the presence of interventionists and a supervision team, whereas the HABIT-ILE@home intervention will take place at the children’s home with the constant presence of a caregiver (eg, parents, relatives, or other close individuals) and intermittent remote supervision. After this high-dosage camp, each group will then be further randomized into 2 subgroups of 11 participants (RCT2). One subgroup will receive the specific HABIT-ILE@home follow-up (5h/wk, for 9 wk), while the other will receive a nonspecific home follow-up based on their usual therapist’s recommendations. Recommendations of practice schedule given to caregivers will be similar for both follow-up groups: 5 hours per week at home for 9 weeks. Participants will be assessed before (T0) and after (T1) the 2 weeks of HABIT-ILE high-dosage camp, as well as at the end of the 9-week follow-up (T2). This study protocol is reported in accordance with the SPIRIT (Standard Protocol Items: Recommendations for Interventional Trials) guidelines (Figure 2).

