### Sample Size

#### RCT1: High-Dosage Intervention (2-Week Home vs On-Site Camp)

Sample size calculation was performed using PASS (version 14.0.15; NCSS) for a one-sided noninferiority *t* test comparing 2 independent means. The analysis was based on the mean improvement in GMFM-66 observed in the study of Bleyenheuft et al [7]. We hypothesized that there would be a true difference of Gross Motor Function Measure (GMFM) units between groups, with an α of .05 and a 1-*β* of 0.9. We estimate that the noninferiority margin (NIM) could reach a maximum of 2 GMFM units since this value is the minimal clinically important difference (MCID) of the GMFM-66. The data are drawn from populations with SDs of 1.9 GMFM units. Consequently, 17 participants are needed per group (N=34). Considering 25% potential dropouts per group, 44 participants will be included.

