#### RCT2: Low- to Moderate-Dosage Home Follow-Up Interventions (9-Week HABIT-ILE@home Follow-Up vs Nonspecific Home Follow-Up)

For RCT2, sample size calculation was also performed using PASS (version 14.0.15; NCSS) for a 2-sided superiority *t* test comparing 2 independent means. The analysis was based on the mean improvement in GMFM-66 observed in the study of Bleyenheuft et al [7]. In that study of school-aged children, the duration of the intervention was 84.5 hours and the GMFM-66 increased by 7 GMFM units. We thus hypothesized that, for 45 hours of intervention, there would be a true difference of 3.75 GMFM units between groups, with an α of .05 and a 1-*β* of 0.8. We estimate that the superiority margin will be 2 GMFM units since this value is the MCID of the GMFM-66. The data are drawn from populations with a SD of 1.9 GMFM units. Consequently, 16 participants are needed per group (N=32). Considering 25% potential dropouts, 40 participants will be included.

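### The RCT2 sample size of 40 does not survive its own 25% dropout allowance, conflicts with the 44 children re-randomised, and leaves its relation to RCT1 losses unstated

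*Protocol article*

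**What the plan says.** All references are to the Protocol article.

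- **Sample Size, RCT2.** The calculation is described as "for a 2-sided superiority" t test. It assumes that "there would be a true difference of 3.75 GMFM units between groups, with an α of .05" "and a 1-*β* of 0.8", with a superiority margin of 2 units and an SD of 1.9. Its result is "Consequently, 16 participants are needed per group (N=32"). The allowance for loss follows: "Considering 25% potential dropouts, 40 participants will be included".
- **Sample Size, RCT1.** The result is "Consequently, 17 participants are needed per group (N=34"), followed by "Considering 25% potential dropouts per group, 44 participants will be included".
- **Study Design.** After the two-week phase, "each group will then be further randomized into 2 subgroups of 11 participants (RCT2"). That is 4 × 11 = 44 children. The Figure 1 legend gives the same numbers, and the two sections describing the follow-up arms each give 22 children.
- **Primary Outcomes, RCT2, and Statistical Analysis, RCT2.** The outcome is the change from T1 to T2, and the T1 value is the covariate in the ANCOVA.

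**The concern.** Three things do not fit together. First, an allowance for 25% loss should be made by dividing the evaluable number by 0.75; the RCT2 figure comes from multiplying by 1.25, which gives too few. Second, the article gives 40 as the RCT2 size in one place and 44 everywhere else. Third, RCT2 is a second randomisation of the same children. A child lost before T1 supplies no observed baseline for RCT2, yet the two 25% allowances stand side by side with no statement of how they relate, and the design sends all 44 into RCT2.

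What is at stake is whether the number of children expected at T2 supports the 80% power claimed for RCT2. As written, a reader cannot tell.

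**Working it through.** **Inputs.** RCT2: 16 per group (32), 25% loss, difference 3.75, margin 2, SD 1.9, α .05, power 0.8. RCT1: 17 per group (34), 25% loss, margin 2, SD 1.9, one-sided α .05, power 0.9. Enrolled and re-randomised: 44. All come from the Sample Size and Study Design sections.

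**1. Reproducing the stated totals**
- RCT2: 32 × 1.25 = 40, exactly as stated.
- RCT1: 17 × 1.25 = 21.25, rounded up to 22 per group, so 44 as stated.

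**2. What those totals leave after 25% loss**
- RCT2: 40 × 0.75 = 30, below 32. The loss that 40 can bear is 1 − 32/40 = 20%.
- RCT2, correct inflation: 32/0.75 = 42.7, so 43. By arm, 16/0.75 = 21.3, so 22 per arm, or 44.
- RCT1: 44 × 0.75 = 33, one below 34. Correct inflation: 34/0.75 = 45.3, so 46.

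**3. The two readings of RCT2 attrition, starting from the 44 enrolled**
- 25% is the total loss from T0 to T2: 44 × 0.75 = 33, which covers 32.
- 25% is lost in RCT1 and a further 25% in RCT2: 44 × 0.75 = 33, then 33 × 0.75 = 24.75, about 25 (12 and 13 per arm).

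**4. Power at these numbers** (exact noncentral t for two independent means, SD 1.9)

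The stated 16 per group is reproduced by testing against the margin, net difference 3.75 − 2 = 1.75, at one-sided .05. On that basis:

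| Evaluable in RCT2 | Where it comes from | Power |
|---|---|---|
| 32 | stated requirement | 0.816 |
| 33 | 44 less 25% in total | 0.827 |
| 30 | 40 less 25% | 0.793 |
| 25 | 44 less two successive 25% losses | 0.722 |

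A two-sided test of a plain 2-unit difference also gives 16 per group. Its power is 0.821 at 32 and 0.712 at 25, so the picture does not depend on which of these two calculations was run.

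For RCT1 (margin 2, true difference taken as 0, one-sided .05), power is 0.913 at 34 and 0.905 at 33, still above the planned 0.90.

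**5. Losses that 44 can bear**
- RCT1: 44 − 34 = 10 by T1, or 10/44 = 22.7%.
- RCT2: 44 − 32 = 12 by T2, or 12/44 = 27.3%.

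**The case against.** The best defence is that the 40 governs nothing. Enrolment is 44 throughout, and 44 is also what correct inflation gives for RCT2 with equal arms. The 40 could be read as RCT2's own minimum, exceeded by what RCT1 required. This holds for RCT2 taken alone, and it is why the multiplication error by itself does no harm if 25% is the total loss. But the sentence says that 40 will be included, not that 40 is a minimum, and its own arithmetic is still wrong.

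A reader might infer that the plan's own assumptions leave RCT2 with about 25 children and clearly too little power. The article does not support that. Nowhere does it say that the two allowances compound, and the 4 × 11 layout does not anticipate only 33 children entering RCT2. The 25 is one end of a range whose other end, 33, meets the requirement.

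A reader might also quote power of 60%: a two-sided .05 test of the net 1.75 gives 0.596 at 25. That mixes in a separate question of sidedness, because the same test has power of only 0.713 at the full 32, before any shortfall.

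Finally, the power loss belongs to the margin-based planning calculation. The ANCOVA in the Statistical Analysis section mentions no margin. On the simple t-test basis, a true difference of 3.75 tested against zero at two-sided .05 keeps power of about 0.997 at 12 and 13 per arm. This limits the consequence, but it does not reconcile the stated numbers.

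Multiple imputation, which the article plans, keeps randomised children in the analysis but does not restore the information that was lost.

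**Conclusion.** The point stands in a limited form. Two parts hold on any reading: 40 does not leave 32 after 25% loss, and 40 contradicts the 44 in the design.

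The third part is an ambiguity with a range. RCT2 has between about 25 and 33 evaluable children under the article's own percentages, with power from about 0.72 to 0.83 against the planned 0.80. That range rests on the one-sided, margin-based calculation and on equal or near-equal arms. The lower end also assumes that the two 25% losses are successive and that a child lost before T1 contributes nothing to RCT2; the second assumption follows from re-randomising after the camp and using a T1 baseline, but the article does not state it.

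The RCT1 slip (33 against 34) is the same error without material effect.

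**What to change.** In Sample Size, RCT2:
- Replace 40 by 44, 22 per follow-up arm, to agree with Study Design and the Figure 1 legend.
- State that RCT2 has no recruitment of its own and draws on the children of RCT1.
- In place of the two separate 25% allowances, give the cumulative loss that the 44 can bear: 10 by T1 (22.7%) for RCT1 and 12 by T2 (27.3%) for RCT2.
- Give RCT2 power under both readings of attrition (33 and about 25 evaluable) and name the calculation used.

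The cost is a few corrected figures and two sentences. The article reports that recruitment and data collection are complete, so no additional enrolment is proposed.

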### Current Status of the Protocol

This protocol was written in 2024, after the study methods had been finalized and recruitment and data collection completed, but before completion of the final statistical analyses.

### Blinding Procedure

External accredited or experienced raters, blinded to group allocation and timing of assessment, will score videos of the main outcome of this multicentric RCT (GMFM-66), as well as one of the secondary outcomes (Both Hands Assessment [BoHA]). Neuroimaging and accelerometers data analyses will also be conducted by raters blinded to group allocation and timing of assessment. Data will be anonymized (using allocation codes) and delivered for analysis after the RCT ends.

### Study Interventions

The intervention is described in accordance with the Template for the Intervention Description and Replication (TIDieR)-telehealth checklist, provided as in Checklist 1 [23].

#### RCT1: High-Dosage Intervention (2-Week Home vs On-Site Camp)

##### Overview

For RCT1, all children will take part in a high-dosage HABIT-ILE intervention, either in an on-site camp or at home with a telerehabilitation program. All children will benefit from 65 hours of therapy at a rate of 6.5 hours per day, 5 days per week, for 2 weeks.

##### HABIT-ILE On-Site Camp (Control Group)

HABIT-ILE therapy for children with bilateral CP aims to improve motor control and coordination of both upper and lower extremities with trunk control in activities of daily living. It is delivered as a 2-week day-camp intervention where each child is trained by 1 interventionist (usually an occupational therapist [OT] or physiotherapist). This therapy is based on MSL principles as the practice is structured (progressive increase of difficulties, segmenting the tasks, and movement abilities), intensive (high therapeutic dosage, high number of movement repetitions, and high motor engagement time), goal-oriented (functional goals set in collaboration with children and their families), “hands off” (ie, therapists adapt the therapeutic environment to allow voluntary motor control rather than guiding movements or passively inducing them), and motivating for the child (activities are fun, set as “games,” with always a positive reinforcement of task performance) (Figure 3). These rehabilitation games always involve bimanual use concomitant with postural request and stimulation of the lower extremities.

**Figure 3. F3:**
[figure not shown]
Activities Performed During an On-Site Hand-Arm Bimanual Intensive Therapy Including Lower Extremities (HABIT-ILE) Camp.

The therapeutic team is coached by trained supervisors (HABIT-ILE experts) who have previously set 5 functional goals for each participant at the end of the first assessment (T0) using the Canadian Occupational Performance Measure (COPM). Throughout the day and during daily team meetings, the supervision team adapts the therapeutic plan and the content of therapeutic sessions to ensure treatment specificity for each child.

##### HABIT-ILE@home (Treatment Group)

HABIT-ILE@home therapy will follow the same MSL principles as the on-site HABIT-ILE camp. The main differences will be the location of the therapy (ie, children’s home) and the person who will accompany the child and deliver the therapy (ie, caregivers who may vary during the therapy if needed). The role of the supervision team will remain crucial in providing remote coaching and guidance to plan the content of therapeutic sessions, adapt the therapeutic plan, and ensure treatment specificity for every child. As the therapeutic background cannot be similar between a caregiver and a therapist (OT and physiotherapist) usually involved in on-site camps, the supervision team will also play a role in coaching caregivers to observe movement abilities and disabilities, detect movement compensations, adapt the therapeutic environment, provide safety, and use positive reinforcement strategies (Figure 4A). To enable caregivers to perform these tasks, various resources will be provided by the supervision team. Before enrollment, families will receive a video detailing the intervention protocol in a child-friendly format, together with written information documents adapted for both adults and children. After enrollment and before the camp, a structured 1-hour training session divided into 2 parts will be given to caregivers. The first part will cover HABIT-ILE principles, including what constitutes bimanual activity and trunk and lower-extremity stimulation, goal setting, the “hands-off” approach, and intensity (high repetition, duration, and motor engagement). Task analysis and shaping will also be explained to help caregivers understand how activities are progressively adapted by the supervision team. Particular attention will be given to maintaining motivation through playful and meaningful activities. Caregivers will be trained on how to deliver feedback (timing, formulation, maintaining positive reinforcement, and avoiding information overload) and on safety (remaining close and vigilant without physically guiding the child to encourage active control while preventing falls). The second part will include theoretical and practical training on the REAtouch Lite device, including navigation of the interface, use of therapeutic games and communication tools, examples of exercises, object presentation and interaction with the screen, completion of activity logs, and daily organization of therapy. A detailed caregiver manual summarizing all elements will be provided. To further help and make the HABIT-ILE@home telerehabilitation program easier to implement, a telerehabilitation device will be delivered to every family. This telerehabilitation device will be the REAtouch Lite (Figure 4B; refer to Multimedia Appendix 1), a lighter and smaller version of REAtouch, a device that has already been used in previous HABIT-ILE on-site camps [24].

**Figure 4. F4:**
[figure not shown]
Home-based supervision and rehabilitation device. (A) Screenshot of a home supervision session during the pilot study. (B) REAtouch Lite rehabilitation device used for home-based training.

The REAtouch Lite contains a wide range of rehabilitative games that can be individualized for each child and provides a visual environment to facilitate caregivers’ decision-making about how to apply MSL principles [24]. The REAtouch Lite is equipped with a telecommunications module for remote communications. In addition to the tablet, a mobile phone used as a microphone and camera and linked to the REAtouch Lite will be supplied. This mobile phone will be used by caregivers to take photos and videos and send them to the supervision team easily. This phone will be supplied with several phone holders, allowing for different camera angles during the supervision sessions. In addition, the mobile phone will enable caregivers to move the camera around the house and outside if required, depending on the functional goals selected. To allow the height of the screen to be adjusted (for postural control and lower-extremity involvement), the REAtouch Lite will also be accompanied by a height-adjustable table. In addition to the REAtouch Lite device, a set of therapeutically useful everyday objects and toys will be delivered to allow caregivers to adapt specifically to the functional goals set (Figure 5A). The therapeutic environment will also be enriched with additional equipment, including an adjustable bench, an inflatable ball, and/or a standing balance board depending on the child’s gross motor abilities and functional goals (Figure 5B).

**Figure 5. F5:**
[figure not shown]
Materials and home therapeutic environment for HABIT-ILE@home therapy. (A) Set of objects made available to children during the 2 weeks of HABIT-ILE@home therapy. (B) Therapeutic environment at home.

To ensure gradual difficulty and specificity during the therapeutic games, 1 hour of remote supervision sessions per day will be planned within the daily 6.5 hours of therapy (30 min in the morning and 30 min at the end of the therapy day; Figure 6). Caregiver competency and fidelity to the intervention will be continuously monitored throughout the intervention. During the first 30-minute daily supervision session in the morning, supervisors will demonstrate how new activities should be implemented, provide guidance regarding task progression and feedback delivery, and ensure caregiver understanding of the proposed activities. During these supervision sessions, supervisors will also provide practical instructions regarding the type of objects to be used, the grasping patterns and positions to encourage, how objects should be presented to the child, and how games should be implemented. Supervisors will additionally answer questions from caregivers and children and provide support and solutions when difficulties arise.

**Figure 6. F6:**
[figure not shown]
Course of a HABIT-ILE@home therapy day. A day of HABIT-ILE@home will begin with 30 minutes of remote supervision via video conferencing software, then the children and their caregivers will be left for 5 hours and 30 minutes in autonomy. Finally, the day will end with another 30 minutes of remote supervision. At the end of the day, the supervisor will send the treatment schedule for the next day.

During the second 30-minute supervision session at the end of the day, caregivers and children will demonstrate the activities performed throughout the intervention day, allowing supervisors to observe implementation, provide individualized feedback, address potential difficulties encountered during therapy, and support collaborative problem-solving strategies. Outside direct supervision sessions, caregivers will be encouraged to record and share videos of therapy sessions using the Axiphone (Axinesis) provided, enabling asynchronous monitoring and additional feedback. These daily interactions between supervisors and caregivers will allow close monitoring of the therapy dose completed and adherence to HABIT-ILE principles. At the end of each therapy day, supervisors will send caregivers a treatment schedule for the following day, including information regarding the type of objects to be used, grasping patterns, object orientation, types of games, and the estimated play time for each game (Figure 6). Fidelity will additionally be supported through individualized daily treatment schedules and activity logs documenting therapy dose and content.

### RCT2: Low- to Moderate-Dosage Home Follow-Up Interventions (9-Week HABIT-ILE@home Follow-Up vs Nonspecific Home Follow-Up)

#### Overview

For the RCT2, all children will take part in a low- to moderate-dosage home follow-up intervention, either with a specific HABIT-ILE@home follow-up or with a nonspecific home follow-up program managed by the children’s usual therapists. In both groups, the follow-up program will last 9 weeks, with a recommendation of 5 hours per week of therapy at home. The 45-hour follow-up dosage (5 h/wk for 9 wk) was selected to provide a feasible home-based intervention for families while remaining comparable to previous HABIT-ILE protocols and above dosage ranges previously associated with clinically meaningful motor improvements in children with CP [13,25]. The amount of therapy time actually spent by the children and the type of exercises actually performed will be documented using the same form in both groups, which families will be asked to complete weekly throughout the 9-week follow-up period. In cases where therapists do not wish to provide a specific home program, families will be offered a home exercise booklet developed by the Fondation Paralysie Cérébrale during the COVID-19 pandemic.

#### Nonspecific Home Follow-Up (Control Group)

For the 22 children who will receive the nonspecific follow-up at home in addition to their usual care, we will contact their usual therapists (OT or physiotherapist) and ask them to create a 5-hour weekly home program based on their usual practice for 9 weeks. This follow-up will correspond to heterogeneous therapist-driven interventions reflecting usual clinical practice, with no standardization of content imposed by the research team. This approach was chosen to reflect real-world clinical settings and the heterogeneity of rehabilitation practices between therapists, while ensuring a comparable amount of therapy time between the HABIT-ILE@home follow-up and nonspecific home follow-up groups.

#### HABIT-ILE@home Follow-Up (Treatment Group)

For the 22 children who will benefit from the HABIT-ILE@home follow-up in addition to their usual care, the treatment modalities will be the same as for the 2-week high-dosage HABIT-ILE@home intervention: it will be delivered at home, with 1 caregiver accompanying 1 child and the use of the REAtouch Lite. There will be 1-hour supervision session per week out of the 5 hours of therapy per week, adaptable according to the children’s and caregivers’ needs. A treatment schedule for 2 weeks will be sent at the beginning of every 2 weeks. The caregiver training, competency assessment, and fidelity monitoring procedures will be identical to those described for the high-dosage HABIT-ILE@home intervention, with the exception that direct remote supervision will be conducted for approximately 1 hour per week instead of daily.

### Data Monitoring Committee

At UCLouvain, there is no data monitoring committee for nondrug interventional studies. However, the Hospital-Faculty Ethics Committee of Saint Luc, composed of a majority of doctors (from UCLouvain or the Cliniques Universitaires de Saint-Luc), an unaffiliated general practitioner, 2 nurses, 3 pharmacists, 2 lawyers, 2 ethicists, 1 methodologist, 1 psychologist, 2 scientific collaborators, 3 patients’ representatives, and 2 healthy volunteers’ representatives, ensures that participants in clinical trials are not exposed to undue risks. The Committee reviews the study protocol and all relevant information regarding experimental treatment to ensure the safety of the research. It also verifies that the information provided to participants is presented in clear, accessible language, allowing them to give fully informed consent. This Ethics Committee operates independently from the study sponsor, with no members affiliated with the research project.

